## Abstract

**Background:**

Sri Lanka (SL) is a multiethnic nation that has endured a decades-long civil war and a devastating tsunami. These events led to a widespread loss of life, displacement, destruction of family and social infrastructure, and economic collapse. Their impact was compounded by adverse social determinants such as poverty, unemployment, food insecurity, and homelessness. Sri Lankan youth are particularly vulnerable to the cumulative effects of these acute and chronic stressors, underscoring the urgent need for interventions that foster resilience and healing.

**Methods:**

We will implement a 10-week school-based program - Leadership, Empathy, Altruism, Personal Growth, and Social Responsibility (LEAPS) - to cultivate character strengths in youth. The program will be culturally and historically tailored to the SL context, and will integrate key tenets from the country’s four major religions to promote unity, social values, and spiritual collaboration. LEAPS will consist of 10 interactive modules delivered through a web-based platform during regular school hours, supplementing the standard curriculum. Teachers will be trained using the train-the-trainer model to facilitate student engagement, ensure program fidelity and long-term sustainability. The impact of LEAPS on student character development and well-being will be evaluated using a cluster randomized pre-post design. Students will be assigned either to the intervention group (where they will participate in the LEAPS program alongside their regular curriculum) or the control group (where they will follow the standard curriculum without additional interventions). Assessments of character strengths and well-being will be conducted via student questionnaires at baseline, post-intervention, and at a 6-month follow-up. Changes over time and between groups will be analyzed to determine program benefits and effectiveness.

**Discussion:**

The LEAPS program aims to enhance character development and well-being in SL youth. The interactive, web-based format of the program is also anticipated to facilitate uptake, knowledge translation, scalability and long-term sustainability, benefiting not only youth but also their families and broader communities.

**Trial registration:**

This trial was registered with the Sri Lanka Trials Registry (No: SLCTR/2020/016) on June 25, 2020.

**Supplementary Information:**

The online version contains supplementary material available at 10.1186/s12889-025-25752-z.

## Background

Sri Lanka, a lower-middle-income country in South Asia, is home to a diverse population of 20 million people, including Sinhalese, Tamils, Moors, and Burghers [1]. Its history has been shaped by both man-made and natural disasters, notably a decades-long civil war and the devastating Indian Ocean Tsunami in 2004. These events resulted in widespread loss of life and displacement, and significantly disrupted the country’s structural and societal developments [2–4].

Young people, who represent nearly a quarter of Sri Lanka’s population, are especially vulnerable to the negative effects of trauma [5–8]. For example, adolescents who survived the 2004 tsunami reported significant emotional and behavioural issues, as well as symptoms of functional impairment that persisted for up to five years post-disaster [9]. Additionally, social adversities like poverty are exacerbated by the country’s ongoing economic and political instability, and further magnified by the lingering impact of past trauma [9]. These challenges underscore the need for evidence-based, cost-effective interventions that support positive youth development (PYD) in Sri Lanka, where such programs remain notably limited. The proposed study aims to address this gap by implementing and evaluating a school-based initiative designed to enhance character strengths and psychosocial competence among Sri Lankan youth.

### Character development

Interventions based on PYD have been shown to help improve health and functional outcomes in youth. Unlike traditional approaches, PYD focuses on cultivating strengths rather than addressing weaknesses [10, 11], thereby fostering positive emotions, cognitive growth, and behavioural improvements [11]. One PYD model specifically targets the development of one or more of the 24 character strengths identified by Peterson and Seligman [12].

Character strengths not only contribute to positive health outcomes but also act as protective factors against the adverse effects of stressful life events, which can compromise mental, physical, and social well-being [13, 14]. For instance, certain character strengths have been linked to accelerated cardiovascular recovery following acute stressors [15]. Several meta-analyses and systematic reviews have demonstrated the benefits of nurturing character strengths, with many school-based programs demonstrating good efficacy and participant engagement [16–19]. One such example is a 12-week intervention conducted in Northern India, where schools aimed to foster character strengths and well-being among 7th- and 8th-grade students. Following the intervention, students in the experimental group reported greater life satisfaction, happiness, and positive affect compared to the control group [20].

### School environments

Schools have proven to be effective and trusted environments for engaging youth and implementing innovative programs, owing to their feasibility, acceptability, adherence, and sustainability [21–24]. Sri Lanka has a well-established school system, encompassing both secular and religious institutions, which has led to growing interest in integrating initiatives that promote the development of character strengths. This approach is grounded in the belief that strong character is essential for personal growth and serves as the foundation of a moral society [25]. Teachers play a pivotal role in nurturing these traits, as they are often trusted figures from whom youth are willing to seek guidance [26].

Effective youth programs also take into account the broader context of youth development, including family, community, and cultural influences. These programs typically build on young people’s strengths and encourage active participation across all components of the initiative. Research highlights the value of an integrated approach that provides support at the community level, such as leadership training and university-community partnerships [27]. However, developing and implementing character strength interventions within educational systems presents challenges, as cultural, environmental, and religious factors shape perceptions of good character, making it difficult for teachers to navigate these complexities [28]. This underscores the importance of adopting context-specific approaches tailored to the unique experiences and needs of Sri Lankan youth.

### Spirituality and its relation to character development

The world’s four largest religions (i.e. Christianity, Islam, Hinduism and Buddhism) account for approximately 75% of global followers. Notably, these same religions are also the most widely practiced in Sri Lanka, albeit in different proportions, with Buddhism having the largest number of adherents followed by Hinduism, Islam and Christianity. One proposed reason for the widespread following of these major religions is their shared emphasis on character development and ethical conduct. A common thread across their teachings of these faiths is the pursuit of self-improvement and a commitment to the ethical treatment of others.

This study involves the development and evaluation of a novel, school-based, and spiritually oriented character development program for early adolescents in Sri Lanka. It will assess the impact of the intervention in promoting values such as understanding, tolerance, empathy, and respect, among others, within a multireligious and multiethnic society.

## Methods

### Study design and study population

The Leadership, Empathy, Altruism, Personal Growth, & Social Responsibility (LEAPS) program will be a school-based intervention that will be implemented and evaluated using a cluster-randomized pre-post study design in the Gampaha district. Gampaha has been selected for its diversity and feasibility. The district offers a multiethnic student population from diverse socioeconomic backgrounds, enhancing the generalizability of the study. Additionally, the presence of the University of Kelaniya within Gampaha ensures proximity and accessibility for researchers, facilitating implementation. The district’s zonal education office has authorized the project and distribution of school invitations. Schools selected for participation possess the necessary IT infrastructure to host the intervention platform. The zonal education office will also obtain approvals from school principals and teachers, and invite students in grades 7–9 (aged 12–14) to participate, ensuring parental consent is obtained beforehand. To participate in the study, students must be able to use web applications and comprehend Sinhalese.

After consent is obtained, ten schools will be randomly assigned (using a computer-generated algorithm) to either receive the intervention or be placed on a waitlist. The intervention group will partake in weekly LEAPS sessions during their IT class periods over a 10-week span. The waitlist group will receive the program 3 months after the intervention group begins the study. Both groups will continue receiving their regular school curriculum throughout the study. Assessments will be conducted at three time points: baseline (t_1_), immediately post-intervention (t_2_, 2.5 months), and 6-months post-intervention (t_3_) (see Fig. 1).

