### Data analysis

Analyses will employ linear mixed-effects models (LMMs) to evaluate changes in VIA-Youth questionnaire and SDQ responses over time and between intervention and control groups, accounting for the nested structure of students within schools. A random intercept for each school will be included to adjust for intra-cluster correlation. Fixed effects will include intervention group, time, student sex, and grade, with interaction terms used to explore whether the intervention effect varies across these factors.

All statistical analyses will be performed using SPSS. The significance level will be set at α = 0.05, and results will be reported with 95% confidence intervals.

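### Both arms have received LEAPS by the 6-month follow-up, so a between-arm contrast at t3 cannot estimate LEAPS versus no LEAPS, yet the plan does not limit the effectiveness contrast to t2

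*Protocol article*

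**What the plan says.** **Schedule (Study design and study population).** The intervention schools have "weekly LEAPS sessions during their IT class periods over a 10-week span". For the control schools: "The waitlist group will receive the program 3 months after the intervention group begins the study". Assessments are at baseline (t1), directly after the intervention at 2.5 months (t2), and six months after the intervention (t3).

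**Control condition (abstract, Methods).** The control group is described as one "where they will follow the standard curriculum without additional interventions".

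**Use of the assessments.** The abstract lists all three assessments and continues: "Changes over time and between groups will be analyzed to determine program benefits and effectiveness". The LEAPS evaluation section likewise names all three administrations as the means of judging programme impact.

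**Model (Data analysis).** Linear mixed models are to evaluate changes in the VIA-Youth and SDQ "over time and between intervention and control groups, accounting for the nested structure of students within schools". On the terms: "Fixed effects will include intervention group, time, student sex, and grade, with interaction terms used to explore" whether the intervention effect varies across these factors. Group is the only treatment term named. No text limits the group contrast to t2, assigns t3 a different role, or says how control-arm data are handled once those schools have had LEAPS.

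**The concern.** A waitlist control supports a randomised treated-versus-untreated comparison only until the waitlist is treated. Here that happens between t2 and t3. Applied as written, the analysis can yield a t3 group difference, or a group effect that includes t3, and either would be read as evidence on effectiveness although the untreated comparator no longer exists.

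The practical risk is misinterpretation. A t3 difference near zero could be reported as an effect that was not sustained, when it would be equally expected if LEAPS worked and lasted in both arms. The abstract adds to the risk, because a reader who relies on its account of the controls would take t3 for a comparison with untreated schools. Once the control schools have had the programme, no later analysis plan can restore the comparison.

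**Working it through.** **1. The plan's own sample size, to see what its power refers to.** Inputs from the power section: d = 0.25, two-sided alpha 0.05, power 0.90, ICC 0.01, 150 students per school, 30% attrition.
- Individual randomisation: 337 per arm, as stated.
- Design effect: 1 + (150 − 1) × 0.01 = 2.49, as stated.
- 337 × 2.49 = 839 per arm, as stated.
- 839 / (1 − 0.30) = 1,199, stated as approximately 1,200.

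The figures reproduce. They assume a difference of 0.25 SD between a treated and an untreated arm.

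**2. Timeline, in months from the start of the intervention arm.**

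| Event | Month |
|---|---|
| t1 | 0 |
| Intervention arm ends LEAPS; t2 | 2.5 |
| Waitlist arm starts LEAPS | 3 |
| Waitlist arm ends LEAPS | 3 + 2.5 = 5.5 |
| t3 | 2.5 + 6 = 8.5 |

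The article rounds 10 weeks to 2.5 months. Taken as 2.3 months, the waitlist arm ends at about month 5.3.
- t2 falls 0.5 month before the waitlist arm starts, so the t2 contrast is clean.
- At t3 the intervention arm is 8.5 − 2.5 = 6 months past programme end, and the waitlist arm 8.5 − 5.5 = 3 months.

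**3. Other readings of t3.**
- Six months from baseline: t3 is at month 6. The waitlist arm finished 0.5 month earlier and the intervention arm 3.5 months earlier.
- Six months from each arm's own programme end (the text does not say this): the waitlist arm is assessed at 5.5 + 6 = 11.5 months. Both arms are again treated.

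**4. Expected t3 contrast.** Let r6 and r3 be the fractions of the effect retained 6 and 3 months after programme end. Then

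t3 contrast = 0.25 × r6 − 0.25 × r3 = 0.25 × (r6 − r3),

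while the effect against an untreated arm would be 0.25 × r6. The documents give no retention rate, so the fading rows are assumptions that show a range.

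| r3 | r6 | t3 contrast (SD) | Effect versus untreated (SD) |
|---|---|---|---|
| 1.00 | 1.00 | 0 | 0.25 |
| 0.90 | 0.80 | −0.025 | 0.20 |
| 0.75 | 0.50 | −0.0625 | 0.125 |
| 0.50 | 0.25 | −0.0625 | 0.0625 |

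The effective size is 839 / 2.49 = 337 per arm. In the first row the chance of a significant t3 difference is 0.05, against 0.90 had the controls stayed untreated. A contrast of −0.0625 has power of about 0.13, in the controls' favour.

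**5. If one group effect were averaged equally over t2 and t3.** With equal persistence, (0.25 + 0) / 2 = 0.125, half the t2 effect. With categorical time crossed with group, the t2 contrast is estimated separately and keeps its value of 0.25.

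**The case against.** The strongest reply is that the article never announces a 6-month between-arm effect. The Data analysis section speaks only of "responses over time and between intervention and control groups" and names neither a primary time point nor a t3 contrast. The design is called pre-post, which fits t1 to t2 as the main comparison. The figure with the assessment schedule is not shown and might indicate that waitlist schools are not assessed at t3. The choice of contrast by visit is often left to the analysis plan. The abstract's description of the controls is accurate up to t2.

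Part of this stands. That t3 enters a between-arm contrast is a reading of the text, though the natural one: the abstract lists three assessments and then says that changes over time and between groups will determine effectiveness. If the waitlist schools are not assessed at t3, there is no treated-versus-treated contrast, but there is also no 6-month between-arm comparison at all. An analysis plan can define the t3 contrast but cannot create an untreated arm that the schedule has removed.

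A reader might also infer stronger things that the documents do not support:
- *That t3 cannot show any difference.* It can, but the difference would reflect time since programme end.
- *That the trial's effect will be halved.* This needs a single group effect pooled equally over t2 and t3, which the article does not specify. A group-by-time model with categorical time leaves t2 intact.
- *That the sign will reverse at t3.* This rests on an assumed rate of fading.

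**Conclusion.** The concern holds as a point about t3 and about how the effectiveness contrast is defined. On every reading of the printed schedule, the control schools have completed LEAPS by t3, so a between-arm difference there does not estimate LEAPS versus no LEAPS. Its expected value is 0 if the effect persists equally in both arms, and it could favour the controls if the effect fades. The 90% power for d = 0.25 can apply only at t2.

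The t1 to t2 comparison is unaffected, so the trial keeps a valid randomised test of the immediate effect. Dilution to about 0.125 is conditional on a pooled group effect. The abstract's account of the controls conflicts with the waitlist delivery in the Study design section and needs correcting. The timeline uses only the article's own dates; equal persistence and the fading rates are assumptions.

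**What to change.** - State in the Data analysis section that the randomised effectiveness contrast is the baseline-adjusted group difference at t2, taken from the group-by-time term with time as categorical or from a model without t3.
- Report t3 as within-arm maintenance, labelled non-randomised, with no between-arm effectiveness claim at six months.
- State that the d = 0.25 and 90% power refer to t2.
- Correct the abstract so that the controls are described as a waitlist that receives LEAPS after t2.
- If a randomised 6-month comparison is intended, the waitlist timing and the t3 timing in the Study design section contradict that aim and must be reconciled before the start.

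The first four changes are wording only. The cost is giving up a 6-month between-arm claim that the present schedule cannot support.

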**Fig. 1 Fig1:**
[figure not shown]
Enrolment, intervention, and assessment schedule for the LEAPS program. Notes. VIA-Youth = Values in Action Inventory for Youth; SDQ = Strengths and Difficulties Questionnaire

### Study aim

The LEAPS program seeks to enhance character development in Sri Lankan youth as a complement to their regular curriculum. It will shift the focus from passive to active learning through student-led, interactive discussions to promote critical thinking. The program emphasizes the shared positive philosophies found in Sri Lanka’s four major religions, using spirituality as a means to foster both social and personal values. The overarching goal of this study is to evaluate the impact of the LEAPS program on character strengths and mental development in youth.

### LEAPS program development

The LEAPS program will consist of interactive sessions that will be designed by a multidisciplinary team of researchers, religious leaders, and clinicians with expertise in youth development in Sri Lanka. A selected software developer will support the program’s technological development and implementation. The unifying moral and spiritual teachings of Sri Lanka’s four major religions will be integrated into the LEAPS curriculum. These teachings will be developed in collaboration with local religious leaders using age-appropriate narratives, images, parables, songs, and other art forms. They will emphasize key character strengths such as tolerance, altruism, respect, kindness, and social responsibility, among others.

The program will be hosted on a user-friendly web platform that provides access to LEAPS materials, interactive games for experiential learning, and online forums for teachers, project teams, and participating students to connect and collaborate. Funding for the development of these materials and digital resources is included in the grant budget. The web application will feature 10 modules focused on character development themes, selected based on the Values-in-Action classification, which outlines 6 core virtues and 24 character strengths (Table 1) [29]. Each module will include 10 interactive segments where students will respond to a statement, paragraph, scenario, image, audio recording or video. Students will receive performance ratings based on their responses and will have the opportunity to retry segments. Upon completing each module, participants will receive a completion award, and at the end of the program, they will be awarded a certificate recognizing their successful completion of the LEAPS character development program.

**Table 1 Tab1:** Values-in-action classification: 6-core virtues and 24-character strengths

Virtues	Character strengths
Wisdom and Knowledge	Creativity, Curiosity, Judgement, Love of Learning, Perspective
Courage	Bravery, Persistence, Honesty, Zest
Humanity	Love, Kindness, Social intelligence
Justice	Teamwork, Fairness, Leadership
Temperance	Forgiveness, Humility, Prudence, Self-Regulation
Transcendence	Appreciation of beauty and excellence, Gratitude, Hope, Humour, Spirituality

Additionally, a comprehensive training manual will be developed and published by the study team for use by teachers supporting the program. The manual will provide an overview of the importance of character development and character strengths, an outline of the LEAPS modules, and an overview of how the program will be evaluated from student responses. Teachers from participating schools will undergo a 3-day training session (3–4 h per day) using the training manual to enhance their ability to support student engagement, module completion and pre-post survey administration. They will also be encouraged and equipped to train their colleagues in the future. These sessions will be led by Sri Lankan and Canadian teams who will use a “train-the-trainer” approach to support high program fidelity and long-term sustainability. Throughout the intervention, teachers will be encouraged to provide feedback on their experiences and student progress to the research team.

### LEAPS evaluation

To determine program impact, student progress and knowledge uptake will be evaluated through scales that will be administered immediately before and after the intervention, as well as at a 6-month follow-up.

Demographic data will be collected at baseline using an online self-reported questionnaire. This will include participant age, sex, academic performance, ethnicity, religion, language proficiency, region of residence, information related to parents and siblings, and future aspirations. This questionnaire will be developed by the study team.

The Values in Action Inventory for Youth (VIA Youth-96) will be adapted and used as the primary efficacy measure to assess changes in student character strengths. This self-administered questionnaire is designed for individuals aged 10–17 years and uses a 5-point Likert scale with both positively and negatively keyed items [29]. Although the scale has been previously adapted for use in diverse communities and cultures, a Sinhalese version is not yet available. In this study, it will be translated into Sinhalese using forward-back translation consistent with WHO guidelines (WHO, 2016). To ensure conceptual and cultural equivalence, the scale will also be adapted through a structured Delphi consensus process, a widely accepted technique for cross-cultural instrument adaptation [30–32]. The Delphi panel will include 30 experts in child and adolescent mental health, education, and community health, including eight board-certified child and adolescent psychiatrists and consultant general adult psychiatrists, as well as pediatricians, community physicians, school counselors, and psychologists. Through multiple iterative rounds, the panel will refine the translated items to enhance cultural relevance, clarity, and developmental appropriateness for Sri Lankan adolescents. Following adaptation, the Sinhalese VIA-Youth will be validated in our sample by assessing reliability, factor structure, and construct validity.

Changes in behavioural and emotional states will be assessed pre- and post-intervention using the self-report version of the Strengths and Difficulties Questionnaire (SDQ), a brief behavioural screening tool. The SDQ includes 25 items across five subscales: emotional symptoms, conduct problems, hyperactivity/inattention, peer relationship problems, and prosocial behaviour. Although the SDQ has been translated and studied in Sri Lankan samples, the psychometric properties varied [33]. Therefore, we will report its reliability, factor structure, and construct validity in our sample. The questionnaire will be administered at each data collection point.

